### 2.3. “PREVIENE-CÁDIZ” [CADIZ-PREVENT] Intervention Protocol

The “PREVIENE-CÁDIZ” [CADIZ-PREVENT] intervention (S1) will have a multimodal nature and will be aimed at schoolchildren, their families and schools. The intervention activities/sessions will be implemented by the teachers at the school centers. The research team will train those teachers to implement the program, and parents in a face-to-face session, but not schoolchildren. To achieve this, before implementing the intervention, the management teams and teachers of the intervention group will receive training sessions managed by the CEP (Center for Teacher Education) of Cádiz from the research team. These sessions will last 10 classroom hours and will be aimed at updating knowledge on promoting healthy lifestyle habits (healthy eating, promoting physical activity, reducing sedentary lifestyle, the importance of sleep and promoting health based on resources). Moreover, the sessions will be addressed for the teaching context, and they will show how to use the tools available to implement the intervention. All the information covered will be made available to the teaching staff through the “Moodle” virtual tool that will allow the research team and teaching staff to be in permanent contact to resolve any possible doubts. There will also be chat tools for management teams and research teams.

The intervention will be implemented in three settings: classroom, family and school. See the description of each setting below.

#### 2.3.1. In the Classroom (Implemented on the Children and Conducted by the Teachers)

It will be a unit of ten health education sessions which will be carried out in the classroom for six months. The teachers in charge of imparting these ten sessions to schoolchildren during the six months will be free to organize the periodicity with which each session is taught, to make it easier for them to combine it with the rest of the content they have to teach. The unit will encompass healthy eating, physical activity habits, reducing sedentary lifestyle and increased sleep, with content based on the healthy eating and physical activity strategies. This content will include (a) nutrition and healthy components of diet and physical activity and the damages of sedentary lifestyle; (b) promotion of the importance of physical activity and participation in sports and recreational activities; (c) review and reduction of the number of weekly hours of sedentary habits; (d) reinforcement of self-concept and body image; (e) importance of sleep and benefits of proper rest; (f) awareness and use of available resources that promote the acquisition of healthy lifestyle habits (Photovoice). Ten sessions will be conducted (Table 1), led by teachers and physical education teachers.

The teachers’ role during the intervention will be planning the timing and distribution of the sessions to be given, as well as conducting these sessions and promoting positive attitudes and opinions regarding food, healthy physical activity, reduction of sedentary lifestyle, and the importance of sleep and use of resources/assets for health available to students. In addition, the Physical Education teachers will promote an activity to improve adherence to physical activity during “Active Recess” breaks.

#### 2.3.2. At the Family Level (with Parents or Caregivers)

The intervention in families will be carried out in three ways: through workshops aimed at parents or caregivers in schools, which will be led by members of the research team based on everyday situations with graphic and audiovisual material. Through a workbook, which will be given by the teachers to the school children, with which parents and children will work together at home to deepen the content of the intervention that the schoolchildren will be seeing in class with the teachers. And through the Photovoice activity, which will consist of taking two photos (jointly at home or outdoors by parents/caregivers and children) one of a resource that encourages healthy eating and another resource that encourages healthy physical activity. Once each child has taken the two photos, they will take them to school and share it, so that all children become aware of the resources they have around them to improve their diet and to promote practice of physical activity. This activity will be explained in detail later.

The workshops aimed at parents given by the research team will take place during one afternoon per school. They will consist of providing parents with skills and strategies to obtain improvements in eating habits, promote healthy meals through cooking workshops, promote the use of health assets available to families, improve the organization and distribution of their children’s free time and improve their children’s sleep habits. This will help children to reduce sedentary habits at home, to increase the practice of sports, recreational and active leisure activities, to improve their eating habits at home and to achieve adequate sleep habits. Table 2 shows how the workshops will be developed and what content each of them will include.

The decision has been made to concentrate all the information in a single afternoon due to the difficulty that parents/caregivers will have to attend school for 3 h in a row, since most of them will work or have obligations and cannot be attending school frequently. In this way, as it is only one day, we will ensure that many more parents attend, that they pay more attention and successfully understand the material. In addition, the information that we intend to give them is not too extensive, so we believe that it can be covered in a single afternoon (3 h). Above all, our intention is to explain what the intervention will consist of, give them basic information on healthy eating, activity physical activity, reduction of sedentary lifestyle and sleep habits, and explain what the exercise booklet and the Photovoice activity consist of, so that they can later spend more time working at home or outdoors with their children.

The role of parents/caregivers during the implementation of the intervention will be to attend the workshops proposed by the research team, to acquire the knowledge that they will later have to share with their children, complete the workbook with them and complete the Photovoice activity. In addition, they will have to encourage healthy eating at home, healthy physical activity, the reduction of sedentary lifestyle and the importance of sleep.

In the case that a family cannot attend the workshop given by the research team, the audiovisual material exhibited in the workshop will be shared with that family. All the information that will be given to the families in the workshop will be summarized in the audiovisual material. Moreover, if any family wants to remember a concept that has been worked on in the workshop, the school will have this material available and will share it to all participating families digitally. In addition, they will be provided with a document through the school in which the nutrition part and the healthy recipes that will be worked on in the healthy cooking workshop will be summarized. This document will be the same that will be provided to families in the workshop. With all this material, families who cannot attend the workshop will be able to acquire sufficient knowledge to successfully exercise their role within the intervention.

#### 2.3.3. At the School Level (with Teachers and the Management Team of the Schools)

In addition to the implementation of the health education unit previously described at the individual level, the intervention in the school environment will involve the main teachers of the participating classrooms, as well as the Physical Education teachers of the centers involved. They will be given training and a guide for teachers will be provided. Moreover, (as indicated in the previous section), the teachers will provide the schoolchildren with a workbook so that they can carry out recreational activities with the family in their time outside of school. Teachers will monitor whether these activities are carried out by reviewing the workbook and, if necessary, by contacting parents. Once the intervention period is over, all participating schools (both those in the intervention group and those in the control group) will be given a report of results and sample teaching guides that they can implement if they wish in subsequent courses.

### 2.4. Procedures and Assessments

#### 2.4.1. Participation of the Schools in Health Promotion Activities

Before the intervention, a questionnaire (S10) created by the research team will be administered to the directors, management teams or teachers of each center. This questionnaire will be used to collect information on whether or not the center currently participates in other health promotion programs, type of program, activities carried out, time spent, among other issues. It is necessary because participation or not in any health promotion program or activity can condition the results of this study. No school will be excluded from the study if it participates in a health promotion program, regardless of whether it belongs to the intervention group or the control group. What will be done, when the analysis is carried out, will be a differentiation into several categories, taking into account in a differentiated way the centers that participate in some of these programs from centers that do not.

#### 2.4.2. Sociodemographic and Socioeconomic Information

Two questionnaires (S2 and S4) will be used to record the sociodemographic and socioeconomic information of both schoolchildren and family members. The questionnaire administered to schoolchildren (S2) will include questions about the number of people they live with at home, who they live with, among others. The questionnaire addressed to parents (S4) will include questions related to the place of birth, educational level, employment situation and occupation, income level, among others. In this way, the sociocultural situation of each participating family will be assessed.

This information will be recorded both before and after the intervention. Before, in the pre-intervention measurements, which will be carried out during the two months before starting the intervention. And later, in the post-intervention measurements, which will take place during the two months after the intervention.

These questionnaires have been adapted from the study “Previene” [Prevent] carried out in Granada [10] and the study “Prevention of childhood obesity in Barcelona” (POIBA) carried out in Barcelona [38], since our project is based on the experiences of these previous studies. The results of the study carried out in Granada have not yet been published, so it is not yet known whether the intervention was effective or not. In the case of Barcelona, the Public Health Agency has published results of the intervention [38], showing that the program is capable of preventing one out of every 3 new cases of childhood obesity, improving eating frequency and behavior, practicing physical activity, habits sedentary and knowledge.

As a result of these interventions, certain aspects will be corrected and the present one will be improved. The main differences will be that in “PREVIENE-CÁDIZ” [CADIZ-PREVENT] more variables will be included in the pre- and post-intervention measures (evaluation of physical activity, physical condition, sedentary lifestyle, breastfeeding, type of childbirth and birth weight). The intervention will be improved, including activities such as “Photovoice”, which will be explained later. Two tools will be included to improve the evaluation of the satisfaction/reaction of schoolchildren, family members, teachers and management teams. These tools will be the “World Cafe”, which will be explained in detail later, and a questionnaire for teachers and management teams. All these aspects were not considered in the previous interventions and have been considered relevant by the research team to include them in this one.

#### 2.4.3. Anthropometric Measurements

Measurements will be taken both before and after the intervention by previously trained research team members, following the standardized International Society for the Advancement of Kinanthropometry (ISAK) procedure [39]. ISAK is an international society dedicated to the study of kinanthropometry, which has created an internationally standardized procedure for taking anthropometric measurements of children and adults.

Body weight will be measured with a mechanical scale sensitive to 100 g (SECA Colorata 760, Hamburg, Germany). Height will be measured using a portable stadiometer with a precision of 0.1 cm (SECA 213, Hamburg, Germany). Body Mass Index (BMI) will be calculated as weight in kilograms divided by height in meters squared and will be used to determine the level of overweight or obesity. If the BMI of the students is between 18.44 and 19.84 according to Cole’s cut-off points [40], they will be considered to be overweight. If the BMI is between 21.60 and 24.00 [40], they will be considered obese. In addition to this formula, the BMI will also be calculated by estimating the percentiles according to their age based on the World Health Organization recommendations.

The skinfold thickness of the triceps and subscapularis will be measured with a caliper with a precision of 0.2 mm (HOLTAIN DIM-98.610ND, London, UK) and will be used to estimate both the percentage of fatty tissue and muscle tissue. For the calculation of the percentage of fatty tissue, the regression equation proposed by Boileau, Lohman and Slaughter [41] will be used. The skinfold thickness of the triceps will also be used as an indicator (proxy) of obesity, considering values greater than 20 mm as obesity, with a sensitivity of 0.79 for the age range of our study [42]. Furthermore, the waist and hip circumferences will be measured with a 1 mm precision tape measure (SECA 201, Hamburg, Germany) and the waist-hip ratio will be calculated. In addition, the waist/height ratio will be calculated as an indicator related to childhood obesity [43].

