The project, which is 80% co-financed by funds from the Andalusian Operational Program FEDER (European Regional Development Fund) 2014–2020, will conduct in accordance with the Declaration of Helsinki. The protocol has been approved by the Andalusian Biomedical Research Ethics Committee, along with approval from the Delegation of Education and Science of the province of Cádiz (PI-0007-2017, 21 March 2018). In order to guarantee this right, the guarantees of confidentiality of the data will be specified in writing to each family, by means of a letter explaining the objectives of the study, requesting their collaboration and the signed consent of participation, as well as the anonymization of the data. Participation will be voluntary and the collection of information from children will be done by the research team at the school. The questionnaires will be answered in the classroom, and a more intimate space available to the school will be used to carry out the anthropometric measurements, such as a support room, the morning classroom, the library or the gym. Schoolchildren who do not have the informed consent signed by their parents or legal guardians will not participate in the study. These schoolchildren who do not participate in the study and belong to the schools of the intervention group will receive the educational component of the intervention but will not undergo to the pre and post intervention evaluations. And the schoolchildren who do not participate in the study and belong to schools of the control group will not undergo to the pre and post intervention evaluations and of course no intervention. The data obtained in this study will be confidential and will be treated in accordance with Organic Law 3/2018, of December 5, on the Protection of Personal Data, Regulation (EU) 2016/679 of the European Parliament and of the Council, of 27 of April 2016 (General Data Protection Regulation), and in accordance with the official document of the Andalusian School of Public Health on the protection of personal data.

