The dependent variables of our study will be BMI, skinfold thickness of the triceps, waist/hip ratio (as anthropometric variables) and the prevalence of overweight and obesity. As surrogate or intermediate variables we will analyze behaviors related to eating, physical activity and sedentary lifestyle, hours of sleep, knowledge and beliefs about eating and physical activity, as well as the physical condition (IFIS) [44,45] of the children.

In the models, possible covariates related to personal, family, school and environment characteristics will be analyzed. Especially will be analyzed: sex, birth weight, breastfeeding, sociodemographic characteristics, family socioeconomic level, level of physical activity and time of sedentary activities of the parents; behavior, knowledge and beliefs about family food and physical activity, participation of the school in the intervention and level of adherence, participation of the center in other health promotion programs, availability or use of the school canteen and the existence of health assets in the environment.

To determine the efficacy of the different components of the intervention, predictive models will be obtained for each of the outcome variables by backward multiple linear regression, in which all possible components are included and are progressively eliminated from lowest to highest contribution. To analyze the specific contribution of a certain component on a dependent variable, the semi-partial correlations will be obtained; this method allows the effect of the component to be controlled to be subtracted from the predictors being treated. The R^2^ values of the components measure their theoretical contribution and allow establishing a theoretical hierarchy among the components that will be used in the regression by blocks; by changing R^2^ the different contributions of the variables will be seen.

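### One research team both delivers the programme and takes the follow-up skinfolds and girths, with no separation of roles and no masking to the school's arm

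*Protocol article*

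**What the plan says.** **Delivery.** Section 2.3 of the protocol article says: "The research team will train those teachers to implement the program, and parents in a face-to-face session, but not schoolchildren". Section 2.3.2 says of the parent workshops: "The workshops aimed at parents given by the research team will take place during one afternoon per school". It adds that they are sessions "which will be led by members of the research team based on everyday situations with graphic and audiovisual material".

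**Measurement.** Section 2.4.3 says: "Measurements will be taken both before and after the intervention by previously trained research team members". It names the ISAK procedure, a hand caliper for skinfolds and a tape for waist and hip. Section 2.1 adds that "the collection of information from children will be done by the research team at the school".

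**Outcomes.** Section 2.5 says: "The dependent variables of our study will be BMI, skinfold thickness of the triceps, waist/hip ratio (as anthropometric variables", followed by the prevalence of overweight and obesity. In section 2.4.3 the triceps skinfold also enters the body-fat estimate and serves as an obesity proxy above 20 mm.

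**Allocation.** Section 2.1 allocates whole schools, 13 per arm. Control schools receive no educational intervention.

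**The concern.** A skinfold depends on the site chosen, the pinch and the moment of reading. A girth depends on where the tape lies and how tightly it is pulled. A measurer who knows the arm, and who worked on the programme in that school, can shift such readings without intending to. Because allocation is by school, anyone who led a school's workshop or trained its teachers knows its arm on arrival.

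A shift that differs between arms would bias the estimated effect. Recruiting more children does not remove it. Modelling the clustering widens the interval but leaves the shift in the estimate. Two of the three continuous anthropometric outcomes are taken by caliper or tape, and the 20 mm cut-off means that small shifts can reclassify children near it.

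**Working it through.** **1. Who does what.** Setting the sections of the protocol article side by side:

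| Task | Assigned to | Section |
|---|---|---|
| Training intervention teachers | Research team | 2.3 |
| Leading parent workshops | Members of the research team | 2.3.2 |
| Classroom sessions for children | Teachers | 2.3.1 |
| Collecting children's data at school | Research team | 2.1 |
| Anthropometry, before and after | Trained research team members | 2.4.3 |
| Moderating the World Cafe (four intervention schools, within two months after the intervention) | Research team | 2.4.10, Table 3 |

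Section 2.6 places teacher training in Phase I, before the Phase II measurements, so the trainers know their schools' arms before any child is measured. No section says that measurers are masked or are different people from those who deliver. The limitations in section 3 do not mention it.

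**2. Which outcomes are exposed.**
- Triceps skinfold, the 20 mm proxy and percent fat: most exposed, because they come from a hand caliper.
- Waist/hip ratio: less exposed, because consistent tape tension affects numerator and denominator and partly cancels.
- BMI and BMI-based prevalence: largely protected, because they come from a scale and a stadiometer.

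**3. The plan's own figure.** For 35% vs 26%, two-sided 5% and 80% power, the mean proportion is 0.305:

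n = [1.96·√(2·0.305·0.695) + 0.8416·√(0.35·0.65 + 0.26·0.74)]² / 0.09² = (1.276 + 0.545)² / 0.0081 ≈ 410 per group.

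This reproduces section 2.2. The figure rests on prevalence, so the present point does not alter it.

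**4. How much a small shift would matter (illustration).** The documents give no SD, ICC or reader error for skinfolds, so the shift b and the ICC are assumptions, shown over a range. Suppose there is no true effect, 450 children per arm in 13 schools, and a difference of b between arms, in SDs of the analysed variable, caused only by reading.

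- Children per school: m = 450/13 = 34.6
- Design effect: DE = 1 + (m − 1)·ICC
- SE = √(2·DE/450)
- False-positive rate = Φ(−1.96 − b/SE) + Φ(−1.96 + b/SE)

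Example with ICC 0.02 and b = 0.10: DE = 1 + 33.6·0.02 = 1.67; SE = √(3.34/450) = 0.086; b/SE = 1.16; rate = 21%.

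| b (SD) | ICC 0 | ICC 0.02 | ICC 0.05 |
|---|---|---|---|
| 0.05 | 12% | 9% | 7% |
| 0.10 | 32% | 21% | 15% |
| 0.20 | 85% | 64% | 45% |

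If the triceps skinfold SD is 5 to 6 mm (assumed), 0.10 SD is 0.5 to 0.6 mm, or 0.5/0.2 = 2.5 to 0.6/0.2 = 3 steps at the caliper's stated 0.2 mm precision.

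**5. Scale against the trial's own target.** On a normal latent scale, 35% vs 26% corresponds to 0.643 − 0.385 = 0.26 SD. A 0.10 SD shift would be 0.10/0.26 = 0.38 of that.

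**The case against.** **The same team need not mean the same people.** This stands as a limit. Section 3 describes a team of more than ten disciplines, and the article never says that a workshop leader measures in that school. But nothing in the article prevents it, and both roles are assigned to one body.

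**A journal article may leave staffing to the full protocol.** Partly right. A duty roster would not be expected here. However, the article itself assigns both jobs to the research team, in a methods section that goes down to instrument models, and it gives training and the ISAK procedure as the safeguards. Those address technique, not knowledge of the arm.

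**The analysis compares changes, so stable operator differences cancel.** Also right, if the same operator measures on both occasions. What remains is a shift between baseline and follow-up that differs by arm, which is what knowledge of the arm could produce.

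**Stronger readings a reader might infer.**
- *Children would answer to please a presenter they know.* Section 2.3 says the team does not train schoolchildren, and teachers give the sessions. Section 2.1 says of the children's questionnaires: "The questionnaires will be answered in the classroom". No section makes a team member a presenter to the children.
- *All self-reported behaviours are affected.* The parent questionnaires are addressed to families, and nothing says the team supervises them.
- *The bias would be several times the expected effect.* That requires setting an assumed skinfold error against the 0.15 kg/m² BMI result that the Introduction cites from a review. These are different outcomes, and the trial's own target is about 0.26 SD.

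**Conclusion.** The point holds for triceps skinfold and the measures derived from it and, more weakly, for waist/hip ratio. As written, the plan lets people who delivered the programme in a school, and so know its arm, take these readings at follow-up.

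It does not show that bias will occur. Its direction, towards the hypothesis, is plausible but not established, and its size cannot be obtained from the documents. The illustration shows only that a shift of 0.10 SD, if present, would lift a nominal 5% error rate to 15–32% for ICCs from 0.05 down to 0. The prevalence comparison behind the sample size is largely unaffected. This should be changed, because the change is cheap and masking cannot be restored after follow-up, but it does not undermine the trial's main comparison.

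**What to change.** In section 2.4.3:

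1. Roster trained team members so that nobody who trained a school's teachers or led its parent workshop takes skinfolds or girths there.
2. Where feasible, do not tell the measurers the school's arm.
3. Send the same measurers to schools of both arms, so that operator and arm are not confounded.
4. Record an operator code for each child at each visit, so that operator can be examined in the skinfold and girth models.

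If there are too few trained measurers, state in the discussion that these outcomes were assessed unmasked. The article counts disciplines, not measurers, so feasibility is for the sponsor to judge.

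The cost is a duty roster, one data field and slightly less flexible scheduling. Masking will be imperfect, since pupils or classroom material may reveal the arm. Role separation and balanced operators still help when that happens.

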## 1. Introduction

The World Health Organization (WHO) considers obesity to be a problem or main issue of concern for public health today in the developed world, due to the high prevalence of this disease in these countries and all the problems it causes. Together with the International Obesity Task Force (IOTF), obesity has been classified as the epidemic of the 21st century [1,2]. The prevalence of this epidemic has increased in Spain by three to four times in the last 20 years and has not only caused a strong impact on chronic diseases, but also on health spending and the quality of life of the population [3]. Moreover, estimates have been made [4] that by 2050, obesity rates in countries of the Organization for Economic Co-operation and Development (OECD) may affect 60% of men, 50% of women and 25% of children.

In a recent study that evaluated the levels of severe obesity in child populations (6–10 years) of 21 European countries, a conclusion was made that it presented a major public health problem for a large number of countries, especially relevant in Bulgaria, Greece, Italy and Spain. This higher prevalence of obesity in southern European countries has been demonstrated in previous research [4,5], estimated at more than 40%. When the prevalence of obesity in these countries is studied specifically (Italy [6], Greece [7] or Spain), the data are confirmed. Particularly in Spain, the Aladdin study [8], which was carried out between November 2015 and March 2016, found for this age group a percentage of 39.3% with overweight or obesity. Of this percentage, 23.2% suffered overweight and 16.1% obese. The obesity was more frequent in boys than girls.

Within Spain, the province of Cádiz (Southwest) has the highest prevalence of overweight and obesity (35% children aged 6–12 years) compared to the rest of Spain, which constitutes a serious health problem in the province that has been increasing in recent years [9]. Researchers from the Andalusian School of Public Health [10] reported a similar prevalence of overweight and obesity (37%) in children aged 8–9 years in Granada (Southeast Spain). This data confirms the need to develop and reinforce public health policies that reduce these numbers.

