## 2. Materials and Methods

### 2.1. Study Design and Participants

The current study will have a quasi-experimental design with a control group, which will be target children enrolled in third grade of primary education from 26 schools of the province of Cádiz. The inclusion criteria that will be used will be: children belonging to the selected school, who are in the third grade of primary school, regardless of their age, who have the informed consent signed by their parents or legal guardians, who respond to the questionnaires and who undergo to the anthropometric measurements. The exclusion criteria will be that these requirements are not met.

The total number of study participants will be between 850 and 900 children. The parents of each schoolchild will be part of that same subject (father, mother and child are the same subject of study). The sample will be divided into two groups, the intervention group and the control group. The intervention group will contain around 450 schoolchildren and will be made up of 13 of the 26 school centers which will participate in the study. In this group, pre-intervention measurements will be performed, which will be explained later. A multimodal intervention will be developed, which will also be explained in detail later. Finally, post-intervention measurements will be made, which will be the same as the pre-intervention measurements. The control group will also contain around 450 schoolchildren and will be made up of the others 13 school centers which will participate in the study. It will be made up of the same number of schoolchildren. The difference with respect to the intervention group will be that the control group will not receive any educational intervention. Only the pre- and post-intervention measurements will be taken, to later compare the results with the intervention group and find out if an effect has emerged or not.

The province of Cádiz will be divided into four areas: Campo de Gibraltar (six schools), Jerez-Costa Noroeste (five schools), Sierra de Cádiz (nine schools) and Bahía de Cádiz-La Janda (six schools) (Figure 1). In each area, there will be between 200 and 300 participants and school centers belonging to both the intervention group and the control group. This division will be made to have a sample that is as representative as possible of the entire province of Cádiz.

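### The BMI rule is written as two closed bands, so a BMI between 19.84 and 21.60 or above 24.00 has no class, and the prevalence endpoint is miscounted if the rule is followed as written

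*Protocol article*

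**What the plan says.** Section 2.4.3 (Anthropometric Measurements) states that BMI "will be used to determine the level of overweight or obesity". The overweight rule starts "If the BMI of the students is between 18.44 and 19.84 according to" the cut-off points of reference [40]. The obesity rule is "If the BMI is between 21.60 and 24.00 [40], they will be considered obese". Neither sentence mentions age or sex. The section then adds that "the BMI will also be calculated by estimating the percentiles according to their age based on the World Health Organization recommendations". It gives no percentile limits for that version and does not connect it to an endpoint.

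Section 2.5 lists among the dependent variables "waist/hip ratio (as anthropometric variables) and the prevalence of overweight and obesity". Section 2.2 sizes the trial on that prevalence: 35% against 26%, 410 children per group. Section 2.1 admits children "who are in the third grade of primary school, regardless of their age".

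**The concern.** A cut-off is a single value at or above which a child belongs to a class. The article gives each class a lower and an upper number and assigns the child when BMI lies between them. Two things follow from the wording alone.

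- **Unclassified children.** The interval from 19.84 to 21.60 has no label, and neither does anything above 24.00. The second omission removes the heaviest children from the obese class.
- **Loss of order.** Class is no longer monotone in BMI. A rise can take a child out of the count, and a fall can bring one in.

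Section 2.5 judges effectiveness by comparing changes in the groups. If the coding followed the text, some worsening would be scored as improvement and some improvement as worsening, in the outcome on which the trial was sized.

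**Working it through.** **1. The plan's own figure.** For two proportions with two-sided 5% error (the article does not state sidedness) and 80% power, pooled variance under the null:

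n = [1.96·√(2·0.305·0.695) + 0.8416·√(0.35·0.65 + 0.26·0.74)]² / 0.09² = (1.276 + 0.545)² / 0.0081 ≈ 410 per group.

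This matches Section 2.2. The sample size formula is not in dispute here. The question is what is counted as a case.

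**2. The bands, with no assumption.**

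| BMI | Class under the written rule |
|---|---|
| below 18.44 | neither |
| 18.44 to 19.84 | overweight |
| 19.84 to 21.60 (1.76 units wide) | none given |
| 21.60 to 24.00 | obese |
| above 24.00 | none given |

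Changes between visits:

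- 19.5 to 20.5: overweight, then uncounted.
- 23.5 to 24.5: obese, then uncounted.
- 24.5 to 23.5: uncounted, then obese.

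**3. Illustration of size.** Inputs: the Introduction's national figures, 39.3% overweight or obese, of which 16.1% obese. Assumptions, not in the documents: BMI is log-normal, and those shares lie exactly at or above 18.44 and 21.60.

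- Normal quantiles: z(0.607) = 0.2715 and z(0.839) = 0.9904.
- s = ln(21.60/18.44) / (0.9904 − 0.2715) = 0.1582 / 0.7189 = 0.220.
- Median = exp(ln 18.44 − 0.2715·0.220) = 17.37.
- P(BMI ≥ 19.84) = 0.273 and P(BMI ≥ 24.00) = 0.071.
- Overweight band: 0.393 − 0.273 = 0.120. Gap: 0.273 − 0.161 = 0.112.
- Obese band: 0.161 − 0.071 = 0.090. Above the ceiling: 0.071.
- Coded prevalence: 0.120 + 0.090 = 0.210, against 0.393.

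**4. Range.** I kept the anchor at 18.44 and 21.60 and varied two things: the shape (log-normal or normal), and the shares (39.3% with 16.1% obese; 35% with 10%, 14.3% or 18% obese). The 14.3% is 35%·16.1/39.3; the 10% and 18% are assumptions. Coded prevalence runs from 16.4% to 21.4%, and 41% to 53% of affected children go uncounted.

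If the shares are placed at the upper ends of the bands instead (19.84 and 24.00), coded prevalence runs from 15.9% to 25.0%. Here the coded count includes children from 18.44 to 19.84 who are not cases under that anchor, so the shortfall is a net figure and not a number of cases lost.

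**5. Possible effect on power.** Suppose, purely as an assumption, that 40% to 60% of cases went uncounted equally in both arms. Then 35% against 26% becomes 21.0% against 15.6% (multiply by 0.6), down to 14.0% against 10.4% (multiply by 0.4). Power at 410 per group, by the same comparison of proportions, falls from 80% to about 52% and 35% respectively.

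**The case against.** The strongest reply is that this is compressed notation. The numbers are attributed to published cut-off points. Two pairs of cut-offs in a condensed article can be read as the range of lower limits across the children studied: overweight from somewhere in 18.44 to 19.84 upward, obese from somewhere in 21.60 to 24.00 upward. On that reading there is no gap, no ceiling and no neglect of age or sex. The reading is plausible, but it is not what the sentences say, and someone coding from the text would produce the bands. If it is what was meant, the correction is the same.

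A second reply is that WHO percentiles by age are also planned. They are offered only as an addition and are not tied to the prevalence endpoint, so they do not repair the stated rule. The reply does have force on one point: an article may leave to a fuller document which of two classifications is primary, so that silence alone would not be a finding.

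Other parts of the defence stand. BMI, triceps skinfold and waist/hip ratio are dependent variables too and are unaffected. Weight and height are recorded, so any miscoding can be undone at analysis.

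A reader might also infer that growth between visits biases the comparison. With a six-month intervention and a two-month window on each side, visits lie about 6 to 10 months apart, and fixed bands do let growth alone change a child's class. But both arms are measured before and after on the same plan, and the documents do not show that this shifts the between-group difference.

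**Conclusion.** The point holds for the rule as written. The gap, the ceiling and the loss of order follow from the text without any assumption. Measured against 18.44 as the lower limit, the written rule understates prevalence whenever any child falls in an unlabelled range, and it can move prevalence in the wrong direction.

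The size is not established. The drop from 39% to about 21% rests on an assumed distribution and on placing national shares at limits that the article does not link to them. A reader might infer that nearly half the cases will be lost, that the 35% and 26% planning figures are void, or that the heaviest children will in fact go uncounted. The documents do not support these as facts. Each depends on the literal coding being carried out, and the first two also depend on a BMI distribution that is not reported. What is supported is that the rule defining the sized outcome is wrong as stated and should be corrected before data are coded.

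**What to change.** Rewrite the two sentences as lower thresholds:

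- Overweight: BMI at or above the child's overweight cut-off and below the obesity cut-off.
- Obese: BMI at or above the child's obesity cut-off, with no upper limit.

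If the paired figures are the range of cut-offs in reference [40] across the children's age and sex, say so, and apply each child's own cut-off at the age of each visit. Name this one classification as the prevalence endpoint and report the WHO percentile version as a sensitivity analysis.

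The cost is two rewritten sentences and a recoding step. Weight and height are measured at both visits and sex is a listed covariate. Date of birth is not named among the items collected, but age is already needed for the WHO percentiles, so confirm that it is recorded at each visit.
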